##### Primary aim and outcome

To ascertain effectiveness of tailored, peer-based sleep health education and social support in increasing adherence rates to recommended OSA evaluation and treatment among blacks at risk for OSA. We hypothesize that greater adherence will be achieved, defined as successful completion of home sleep study and sleep clinic assessment.

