### Study rationale

The primary aim of this trial is to ascertain (1) the effectiveness of tailored, peer-based sleep health education and social support in increasing adherence rates to recommended OSA evaluation (adherence to sleep home-based study is categorized as ‘yes’ or ‘no’ depending on whether the individual participated in a sleep home-based study and adherence to sleep clinic assessment is categorized as ‘yes’ or ‘no’ depending on whether the individual had a laboratory-based sleep clinic assessment) and treatment among blacks at risk for OSA (adherence will be defined as whether the participant wore their CPAP device > 4 hours a night for 70% of the nights); and (2) the rate of OSA among black men and women at the community level using home-based sleep recordings. Early identification of OSA via home-based studies in this high-risk population could potentially lead to early OSA treatment and prevention and may reduce subsequent health consequences such as CVD and premature death. Our study can be used as a national model for how to increase racial/ethnic minority engagement in the healthcare system through culturally responsive strategies that bridge underserved communities. Thus, our proposal to screen blacks in community settings, such as barbershops, beauty salons, and places of worship, will maximize the likelihood of recruiting and enrolling a representative sample of blacks.

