### Phase III: OSA assessment and diagnosis – home study and sleep clinic assessments and treatment customization

#### Primary trial outcome: sleep home study

The research staff will conduct an 8-day home study to collect sleep data via actigraphy (ActiGraph WGT3X-BT monitor) and a daily sleep diary, as well as environmental influences of sleep, such as noise and temperature, two factors that may confound sleep duration and quality. On day 1 of home sleep, a study technician will visit the participant’s home to place the ActiGraph watch on the participant’s wrist as well as connect a sound device and thermometer to capture the participant’s physical sleep environment. During the visit at the participant’s home, staff will demonstrate how the WatchPAT™ home sleep test device is used, worn on the wrist and fingertip on the last night of a 7-day sleep diary. On the seventh day of the home evaluation, the study’s technician will re-visit the participant’s home to set-up a device, the WatchPAT™ portable sleep test device to determine the severity of OSA risk. The WatchPAT™ is an in-home device utilized for OSA evaluation cleared by the Food and Drug Administration and approved by the Center for Medicare & Medicaid Services [93, 94]. It measures blood oxygen saturation, pulse rate, airflow, respiratory effort (a combined signal using pressure transducer sensing forehead venous pressure, venous volume by photoplethysmography), and snoring levels. Automated analysis of physiologic data yields OSA indices that reflect OSA risk, which is verified by a trained human scorer to ensure accuracy of signal interpretation. The device integrates physiologic, clinical, and anthropomorphic data to determine the presence and severity of OSA. Correlation between the WatchPAT 200 and PSG recordings was 0.96 using AHI with a 4% desaturation. Diagnostic sensitivity and specificity of in-home WatchPAT using AHI ≥ 15 (in the absence of OSA symptoms) are 0.85 and 0.91, respectively [93]. Based on Medicare guidelines [95], those with an AHI ≥ 10 will be referred for treatment (American Academy of Sleep Medicine guidelines) [96]. We chose this criterion to ensure that we reduce the rate of false negative results. In the 7-day sleep diary, participants will indicate (1) nap time and duration, (2) medications/drugs promoting night-time sleep or daytime alertness (e.g., caffeine), (3) time to bed, (4) time of lights off, (5) final time of awakening, (6) final time of arising, and estimated (7) sleep latency, (8) sleep duration, (9) wake after sleep onset, (10) sleep quality, and (11) daytime sleepiness. On day 8, the study staff will retrieve all devices and data from the sleep diary.

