
After the home sleep study, the study staff will provide the results to the study physician to determine the risk of sleep apnea from the WatchPAT™ home sleep recorder device. The study physician will discuss the home study results with all participants and will recommend treatment to those meeting OSA diagnostic criteria (AHI > 10). Participants who do not meet OSA diagnostic criteria will be transferred to the project coordinator either for study close-out since they no longer need to continue their participation in the study, for future clinic-based diagnostic assessment, or for treatment customization. Participants who are at risk for OSA will be referred for further diagnostic assessment and treatment to a sleep clinic accredited by the American Academy of Sleep Medicine. Expenses incurred from laboratory and CPAP procedures recommended by sleep clinicians in our catchment area will be billed directly to the participant’s insurance. In the rare instance that a participant might fail to obtain insurance, the study project will absorb some medical costs and a CPAP device will be dispensed as an in-kind contribution.

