#### Secondary trial outcome: sleep clinic assessment, diagnosis, and treatment customization

Participants who have a high AHI (≥ 10) will be referred for sleep assessment to determine OSA diagnosis and appropriate treatment. Peer health educators will support participants as they navigate this phase of their care by helping them with scheduling appointments and occasionally accompanying them to appointments if requested by the participant, as well as providing general information about the sleep assessment. The purpose of this level of social support is to demystify the OSA assessment (which includes self-report screener, home study, and clinic study using polysomnography) experience, which can be daunting and might deter participants from undergoing the sleep assessment. In our previous research, we found that blacks were less likely to adhere to recommended OSA treatment and therefore the use of peer health educators is a practical way of increasing CPAP adherence.

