#### Sample size and power analysis

We plan to screen approximately 1250 blacks in the community. Assuming 39% of blacks are at risk for OSA, we propose to enroll 398 men and women (199 per study arm). With a 35% attrition rate, 258 will have provided adherence data during 6-month follow-up assessment. Based on the pilot data, we expect that 41% in the intervention arm (*n* = 82) and 26% in the attention-control arm (*n* = 52) will have completed all aspects of the trial, including site interview, home evaluation, and follow-up assessment (Fig. 2).

The primary study outcome is receipt of home OSA evaluation after tailored peer-based sleep health education. Data obtained from a sample of blacks provided a current estimate of the likely OSA evaluation rate we expect in the partner community. Analysis showed that 41% of participants adhered to recommended OSA evaluation after intervention exposure, whereas 26% of participants in a control group agreed to undergo evaluation. These preliminary findings represent the likely adherence rates expected in our proposed study.

We propose to achieve an evaluation rate in our intervention arm of 41% based our pilot study mentioned above. This would represent a 63% greater adherence rate compared with controls, which potentially would have a significant public health impact. Assuming a 15% increase in the likelihood of undergoing home-based OSA evaluation, a standard error of 0.09% and a sample size of 398, the study will be adequately powered (> 85%) to detect a significant increase in adherence. Specifically, an observed difference of 15% would be reported with a 95% CI 7–24%. A two-tailed test, with 80% power and α = 0.035 comparing adherence rates of 26% with 41% requires 199 participants per group. Of note, our sample size estimate adjusted for potential intra-cluster coefficient that may be observed in both the treatment and control arms, which according to our initial pilot was 0.014. The resulting effective sample size (*ESS = [M x K/DE]*) after adjustment for design effect (*DE*)… [*DE = 1 + (n-1)ρ*] was *n* = 398 (199 participants per arm) [97, 98]. The study is also powered to assess differences in adherence rates to CPAP treatment between the two arms considering the likely attrition rate of 35% during follow-up assessment.

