#### Statistical analysis plan

To describe sample characteristics, we will use measures of central tendencies and dispersion for continuous data; frequency distributions will be used for categorical data. We will use χ^2^ tests to compare categorical data and GEE to examine relationships between predictors of adherence to OSA evaluation and/or treatment. The main dependent measure will be adherence to OSA evaluation (yes vs. no) and adherence to CPAP treatment (yes vs. no). Effects of sociodemographic and clinical factors will be adjusted. MANCOVA will be used to assess differences between baseline and 6- and 12-month subjective measures (e.g., self-efficacy, apnea knowledge, functional outcomes in sleep). Structural Equation Modeling will be used to examine the path toward adherence to OSA evaluation and/or CPAP treatment, considering the contributions of candidate factors.

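### The primary outcome is home sleep study alone in two places and home study plus clinic assessment in a third; read literally, the second version scores some home-study completers who test negative as non-adherent

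*Protocol article*

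**What the plan says.** All references are to the protocol article.

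- **Phase III, first outcome heading:** "Primary trial outcome: sleep home study".
- **Sample size and power analysis:** "The primary study outcome is receipt of home OSA evaluation after tailored peer-based sleep health education". The rates of 41% and 26%, and the power claim, are attached to this outcome.
- **Phase III, second outcome heading:** "Secondary trial outcome: sleep clinic assessment, diagnosis, and treatment customization". The Phase IV heading then ranks CPAP adherence third.
- **Primary aim and outcome:** "We hypothesize that greater adherence will be achieved, defined as successful completion of home sleep study and sleep clinic assessment".
- **Statistical analysis plan, opening paragraph:** "The main dependent measure will be adherence to OSA evaluation (yes vs. no) and adherence to CPAP treatment (yes vs. no".
- **Study rationale:** clinic adherence is coded yes or no "depending on whether the individual had a laboratory-based sleep clinic assessment". There is no category for people who were not referred.
- **Who goes to the clinic:** under the secondary outcome heading, participants with a home AHI of 10 or more "will be referred for sleep assessment to determine OSA diagnosis and appropriate treatment". Those who do not meet the diagnostic criteria pass to the project coordinator, "either for study close-out since they no longer need to continue their participation in the study", or for later clinic-based assessment or treatment customization.
- **Analysis under the primary aim:** intention to treat, with GEE on receipt of OSA evaluation, which is not defined further there.

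**The concern.** Clinic assessment is both a secondary outcome and a required part of the definition given under the primary aim. A trial analysed on one definition has a different numerator, different expected rates and different power from a trial analysed on the other. The article gives no rule for choosing between them. That leaves room to settle the primary after the data are seen.

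The two-part definition also has a structural fault. The second step is offered on the strength of the first step's result, so whether a participant can score as adherent depends partly on disease status. A participant who completed the home study, tested negative and was closed out did everything asked and still counts as a failure. If the intervention raises home-study uptake, more such people arise in the intervention arm, and the absolute difference between arms shrinks.

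**Working it through.** **1. The plan's own figures.** Inputs from the sample size section: 41% vs 26%, 199 per arm, two-sided alpha 0.035.

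Power = Φ{[d√n − z√(2p̄(1−p̄))] / √(p₁(1−p₁) + p₂(1−p₂))}, with d = 0.15, p̄ = 0.335, z = 2.108.

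- d√n = 0.15 × √199 = 2.116
- z√(2 × 0.335 × 0.665) = 2.108 × 0.6675 = 1.407
- √(0.41 × 0.59 + 0.26 × 0.74) = 0.659
- (2.116 − 1.407) / 0.659 = 1.075, so power = 85.9%

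The claim of more than 85% reproduces for the home study, without a design effect. The 199 per arm does not follow from 80% power and alpha 0.035 alone, which give 172, or 185 with continuity correction. A design effect could close the gap, but its cluster size is not stated, so 199 is neither confirmed nor shown to be wrong. The present point does not depend on it.

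**2. The two-part definition over all randomised participants.** Let q be the share of home-study completers who are positive and c the share of those who attend the clinic, both assumed equal in the two arms. The composite rates are 0.41·q·c and 0.26·q·c.

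Where the assumed values come from:
- q = 0.90: share diagnosed among those evaluated in an earlier study (Background).
- q = 0.594: implied by the stated ARES sensitivity of 0.94 and specificity of 0.79, if the 39% described as at risk is taken as the screen-positive rate. Prevalence = (0.39 − 0.21) / (0.94 − 0.21) = 0.247, and 0.94 × 0.247 / 0.39 = 0.594. The article also quotes a positive predictive value of 0.91, which is close to the upper value. These ARES figures refer to AHI > 5, whereas clinic referral uses 10, so neither is the referred share itself.
- c = 0.38: adherence to physician-recommended sleep evaluation in community clinics (Background).
- c = 0.60 and c = 1.00: illustrative, with no source in the article.

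Power at 199 per arm, alpha 0.035, same formula:

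| q | c | Intervention | Control | Power |
|---|---|---|---|---|
| home study alone | – | 41.0% | 26.0% | 85.9% |
| 0.90 | 1.00 | 36.9% | 23.4% | 79.8% |
| 0.594 | 1.00 | 24.4% | 15.4% | 54.7% |
| 0.594 | 0.60 | 14.6% | 9.3% | 32.1% |
| 0.594 | 0.38 | 9.3% | 5.9% | 20.3% |

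In the rows with c = 1.00, the whole loss comes from scoring negatives as failures. In the last two rows, part of it is real non-attendance among people who were referred.

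**3. How many completers are affected.** Expected completers are 199 × 0.41 ≈ 82 and 199 × 0.26 ≈ 52. The number failing only because they tested negative, if none of them is sent to a clinic, is (1 − q) times these: about 8 and 5 at q = 0.90, and about 33 and 21 at q = 0.594. The ratio of rates stays at 41/26 = 1.58 under equal shares. What shrinks is the absolute difference, from 15 points to between 13.5 and 3.4.

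**The case against.** The ranking is clearer than a bare list of conflicts suggests. Three headings put the home study first, the clinic second and CPAP third. The sample size section names the home study outright, and the CPAP hypothesis and its analysis sit under the secondary aim. The sentence about the main dependent measure opens the whole analysis section, so it is weaker evidence of a rival primary. This stands: the definition under the primary aim is the main outlier. It is still the definition printed under that heading, and nothing in the article says that the other sections override it.

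The definition could also be read as two separate outcomes, or as requiring the clinic only where the clinic was recommended. Both readings are possible, but neither is stated.

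A reader might infer that no OSA-negative participant could ever count as adherent. The documents do not support that, because later clinic-based assessment is listed alongside close-out. The fault concerns negatives who are closed out or otherwise not sent to a clinic.

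A reader might also infer that the primary time point shifts between 6 and 12 months. It does not: the Methods section ascertains all outcomes at both, and the 6-month figure in the sample size section is an attrition count. The contrast between having taken part in a home study and having completed one is a difference of wording that adds little.

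Finally, the 41% and 26% come from a pilot that measured making an appointment. They are a proxy for home-study completion too. The comparison above shows what the definition does to power given the plan's own rates; it does not validate those rates.

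**Conclusion.** The contradiction is on the page and must be resolved before outcomes are analysed. It is not detail left to a fuller document, since the article itself states definitions that cannot all be the primary. Taken literally under intention to treat, the two-part definition misclassifies home-study completers who test negative and are not sent to a clinic.

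The stated power applies to the home study only. For the composite, the illustration runs from about 80% to about 20% at the plan's alpha of 0.035. That range rests on assumed positive and attendance shares, on their equality across arms, on all randomised participants being the denominator, on no completer who tests negative reaching a clinic, and on no design effect. The direction of the effect is secure; its size is not, because the article gives no positive share at the referral cut-off and no clinic attendance rate for this pathway.

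**What to change.** Amend the primary aim section and the opening of the statistical analysis plan to match the Phase III heading and the sample size section:

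1. One primary outcome: home sleep study completed (yes/no) by the 12-month assessment, with all randomised participants in the denominator and no study counted as no. The 12-month point is a choice within the existing follow-up schedule and should be stated.
2. Keep clinic assessment secondary and CPAP adherence third, as the headings already rank them.
3. For each of these two, state how participants who were not referred, or not prescribed CPAP, are scored. If all randomised participants stay in the denominator, report the result as the rate of reaching that step of care and not as adherence, because people who were never offered the step would otherwise again be labelled non-adherent.
4. Use the same term for the primary outcome in the GEE paragraph.

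The cost is a wording amendment with no new data or procedures. The article reports recruitment as ongoing. It should be made before any outcome comparison is seen.

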##### Analysis

We will perform analysis on an intention-to-treat basis. We will assume participants in the intervention arm to have received the full intervention dose and those in the control arm to have received no tailored education. Prior to testing for intervention effects, we will verify comparability of the intervention and control arms with respect to all available sociodemographic data using *t* tests and χ^2^ tests. GEE methods will be used to estimate the odds associated with receipt of OSA evaluation contrasting the two study groups. GEE is preferred over standard logistic regression, as it adjusts for clustering effects. Delays in receipt of endpoint (OSA evaluation or treatment) will be adjusted in the models. Since the type of health educator may influence our findings, we will perform statistical analyses that will detect any potential confounding effect that health educator assignment may have on outcomes. This type of method is distinguishable from a traditional cluster randomized trial as the unit of randomization is at the individual/participant level and not groups of individuals.

##### Secondary aim

To ascertain how many among black men and women have OSA or are at risk for OSA at the community level using home-based sleep recordings in accordance with criteria from the American Academy of Sleep Medicine. We hypothesize greater adherence to OSA treatment using telemetry (CPAP use; > 4 hours a night for 70% of the nights) [99–101].

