##### Eligibility criteria (inclusion and exclusion)

Eligible participants will (1) self-report their race/ethnicity as black, African American, or African ancestry; (2) be ≥ 18 years old; (3) accessible by telephone or cellphone; (4) have no plans to move away from the region within the year following enrollment; (5) consent to participate in the study, which includes permission to release medical record information; and (6) have a positive screening for OSA, based on whether an individual receives a score ≥ 6 on the ARES Questionnaire. Participants are ineligible if they (1) are involved in another sleep study; (2) know someone who is participating in this study; (3) plan to move away in the next year; (4) had a heart attack or stroke within the past 12 weeks; (5) are pregnant; (6) refuse to use the ActiGraph activity monitor; (7) are non-English speaking; or (8) refuse to use the WatchPAT™ home sleep test device. Participants who are currently being treated for sleep apnea will not be eligible for the study. We do not anticipate that concomitant treatment for other medical conditions will preclude participation in the study.

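### The aim promises a community-level OSA rate, but home recordings come only from ARES-positive enrolled participants who complete the home study, so the observed proportion would overstate the rate in the screened community roughly two-fold

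*Protocol article*

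**What the plan says.** The Study rationale gives two parts to the primary aim. The second is "the rate of OSA among black men and women at the community level using home-based sleep recordings". The Secondary aim repeats it as "how many among black men and women have OSA or are at risk for OSA at the community level using home-based sleep recordings". The Background says that the true prevalence in a community sample of urban blacks is unclear and offers this as a reason for the study.

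Under Eligibility criteria, a participant must "have a positive screening for OSA, based on whether an individual receives a score ≥ 6 on the ARES Questionnaire". People who "refuse to use the WatchPAT™ home sleep test device" are ineligible, and the same section adds: "Participants who are currently being treated for sleep apnea will not be eligible for the study".

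The sample size section plans to screen about 1250 people and continues: "Assuming 39% of blacks are at risk for OSA, we propose to enroll 398 men and women". It expects 82 intervention and 52 control participants to complete all aspects of the trial, home evaluation included. The same 41% and 26% serve there as the expected home-evaluation rates.

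Data collection and management names a Heckman two-stage approach, EM-type methods, a comparison of non-participants with participants, and a comparison of withdrawals with completers.

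**The concern.** The population named in the aim and the population that is recorded are different. A rate at community level needs information on people who screen negative as well as positive. On the plan's own assumption, 100% − 39% = 61% of those screened are ARES-negative and never receive a home recording. Selecting on a questionnaire built to detect OSA raises the proportion with OSA among those recorded, so the trial would report the yield of a screening step under the name of a prevalence.

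The figure could be taken at face value, because the article presents the community prevalence as an open question and expects its recruitment to give a representative sample. No analysis of the enrolled participants' recordings alone can supply what is missing on screen-negatives. This is therefore a matter of how the aim is stated, not of detail left to a fuller document.

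**Working it through.** **Inputs**
- Share screening positive, q = 0.39 (sample size section). It is stated there as the share at risk; the Background says that risk in this study is defined by the ARES score.
- ARES sensitivity Se = 0.94, specificity Sp = 0.79, PPV 0.91, NPV 0.86 (ARES questionnaire section; Se and Sp at AHI > 5).
- Expected completers: 82 + 52 = 134 of 398, or 34%.
- WatchPAT sensitivity 0.85 and specificity 0.91 (sleep home study section; at AHI ≥ 15).

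The plan states no community rate to reproduce, so the first check is whether its four ARES figures agree.

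**Step 1: consistency of the ARES figures.** With PPV = Se·p / [Se·p + (1−Sp)(1−p)], PPV 0.91 requires a prevalence p = 0.693, where NPV is 0.854. NPV 0.86 requires p = 0.682, where PPV is 0.906. The four figures agree with each other at a prevalence of about 0.69. At that prevalence about 72% of people would screen positive (0.94 × 0.693 + 0.21 × 0.307 = 0.716), not 39%. The printed PPV and NPV therefore do not carry over to this screened population.

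**Step 2: the rate implied by 39% positive.** From q = Se·p + (1−Sp)(1−p):
- Screened community: p = (0.39 − 0.21) / (0.94 − 0.21) = 0.247.
- Among ARES-positives: 0.94 × 0.247 / 0.39 = 0.594.
- Ratio: 0.594 / 0.247 = Se/q = 0.94 / 0.39 = 2.41.

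If 39% holds, ARES selection alone cannot push the ratio above 1/0.39 = 2.56. The ratio falls below 2 only if sensitivity is under 0.78.

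**Step 3: one assumption varied at a time, from the base of 2.41**

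| Variation | Ratio |
|---|---|
| ARES-positive share 31.8% (398/1250) | 2.96 |
| ARES-positive share 45% / 50% (assumed) | 2.09 / 1.88 |
| 10% of the community already treated, all with OSA (assumed): 0.594 / (0.247 × 0.9 + 0.1) | 1.85 |
| WatchPAT error in the observed yield: (0.85 × 0.594 + 0.09 × 0.406) / 0.247 | 2.20 |
| Completion among those with OSA relative to those without: 0.5 / 0.8 (assumed) | 1.71 / 2.19 |
| The same, 1.5 / 2 (assumed) | 2.79 / 3.02 |

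The range is about 1.7 to 3.0.

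**Step 4: OSA rate among screen-negatives.** With p = 0.247, 1 − NPV = 0.06 × 0.247 / 0.61 = 0.024. The printed NPV would give 0.14.

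**The case against.** The strongest defence has three parts.

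First, the plan does deal with selection. Data collection and management names methods for refusal, attrition and missing data and undertakes corrections to improve generalisability. A reader might infer that nothing in the plan addresses selection, and the document does not support that. What stands is narrower: those methods concern people who refuse or drop out, not people excluded by the ARES criterion.

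Second, the analysis paragraph under the Secondary aim describes only a GEE for CPAP adherence, but a journal article may leave the estimator of a descriptive proportion to a fuller document. That is fair, and the silence is not the point here. The point is the population that the aim names.

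Third, community level could mean the setting (barbershops, salons, churches) as opposed to a clinic, and the at-risk part of the aim could be answered from the questionnaire in all those screened. But both statements of the aim tie the result to home recordings, the Background speaks of actual prevalence, and the Study rationale expects a representative sample. The setting reading does not fit these. The abstract's mention of participants at low to high risk does not help either, since the eligibility criterion governs enrolment.

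On size, a reader might infer that the overstatement is at least two-fold and that selection of completers adds to it. Neither is supported. Excluding treated OSA lowers the observed rate, the direction of completer selection is not given, and several variations fall below 2. A reader might also apply the printed PPV and NPV at 39% positive, obtaining 91% against 0.39 × 0.91 + 0.61 × 0.14 = 44%, and treat this as a second confirmation. It is not: at 44% prevalence the stated sensitivity and specificity would make 0.94 × 0.44 + 0.21 × 0.56 = 53% screen positive.

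**Conclusion.** The concern holds. The aim names a community rate, while the design yields the proportion with OSA among ARES-positive, device-accepting, untreated participants who complete the home study. On the plan's own 39%, sensitivity and specificity, that proportion is about 59% against about 25% in the screened community, roughly a two-fold overstatement (2.4).

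The result rests on three assumptions: that 39% is the ARES-positive share, that the quoted ARES accuracy applies in this population, and that one AHI cut-off serves throughout. The last is not so in the text: ARES accuracy is quoted at AHI > 5, WatchPAT accuracy at AHI ≥ 15, and home-study referral is at AHI ≥ 10. The range of 1.7 to 3.0 comes from single assumed variations and is not a confidence interval.

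The randomised comparison and its power are untouched. What changes is the conclusion that the trial can draw on a stated descriptive aim.

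**What to change.** Reword the aim in both the Study rationale and the Secondary aim: the proportion with home-study AHI in the OSA range among ARES-positive participants who complete the home study.

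If a community figure is wanted, report it separately as model-based:

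- Estimate = (screen-positive share of the roughly 1250 screened × observed yield) + (screen-negative share × assumed OSA rate in screen-negatives).
- Vary the last term from about 2% (Step 4) to 14% (printed NPV), and do not centre it on 14%. With a yield of 59.4% this gives 0.39 × 0.594 + 0.61 × 0.024 = 24.6% (24.7% unrounded) to 0.39 × 0.594 + 0.61 × 0.14 = 31.7%.
- Use one stated AHI cut-off throughout. The 2% to 14% range belongs to AHI > 5 and must be restated for any other.
- Weight completers to all enrolled on baseline data, which fits with the selection methods already named.

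The cost is rewording and one calculation from data already collected. The downside is a less sweeping claim, and a community figure that rests partly on an assumption about people who were never recorded.
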